### Study population

Eligibility criteria are detailed in Table 1. More specifically, the targeted patients had to carry up to 3 brain metastases of solid tumor [16, 17], measuring 5–30 mm in diameter, eligible to stereotactic radiotherapy, of which at least one lesion presented signs of intra-tumor bleeding [18] before stereotactic irradiation.

**Table 1 Tab1:** Study eligibility criteria

Inclusion criteria	- Age > 18 years old - WHO performance status 0 or 1 - Patient having less than 4 brain metastases of solid tumour with a histologically proven diagnosis of solid tumour; patients who have had a metastasectomy and having 1 to 3 brain metastases are eligible; - Brain(s) lesion(s) measuring between 5 and 30 mm in diameter - Patient eligible for stereotactic radiotherapy after a local multidisciplinary committee decision - Signs of intra-tumour bleeding before stereotactic irradiation in at least one brain metastasis and defined on the presence of at least one of these criteria: • Spontaneous high-density lesion on brain CT scan without injection • Spontaneous hyper-intense lesion on brain MRI sequences: on T1 sequence • Lesion with hypo signal on T2* sequences - Patients with an extra-cranial control disease treated with systemic therapy (chemotherapy, immunotherapy or targeted therapy) could be included only if they show a: • complete response disease • partial response or stable disease for more than 3 months - Patient sufficiently cooperating to perform the treatment with the use of a thermoformed mask; - Patient whose neuropsychological abilities allow to follow the requirements of the protocol; - Signed informed consent.
Exclusion criteria	- Patients with small cell lung cancer, germ-cell tumors, lymphoma, melanoma, leukemia and multiple myeloma are not eligible; - Patients with an associated neurodegenerative disease; - Any symptoms not attributable to brain metastasis or cancer disease requiring long term corticosteroid use (regardless of dose); - Contraindication to perform the brain MRI, or to infuse gadolinium or iodinated contrast product - Bleeding disorders; - Genetic disorder leading to hyper radiosensitivity (Neurofibromatosis, ataxia-telangiectasia ...); - Thrombocytopenia < 100,000 cells / mm3; - Anticoagulant therapy with curative intent dosing (deep vein thrombosis …), and/or anti-platelet aggregation during FSRT - Hemorrhagic metastasis of the brainstem; - Patients for whom a treatment plan dedicated to one of the metastasis delivers more than 5 Gy on the other brain metastasis; - Patients with previous brain stereotactic irradiation - Whole brain irradiation history; - Progressive extracranial disease; - Any geographical conditions, social and associated psychopathology that may compromise the patient’s ability to participate in the study; - Participation in a therapeutic trial for less than 30 days; - Patient deprived of liberty or under guardianship.

### Trial design

The study protocol and this manuscript have been written in accordance with standard protocol items, namely recommendations for interventional trials (SPIRIT).

The STEREO-HBM study is a multicenter 2-step non-randomised phase II trial where 46 patients are planned to be enrolled (Fig. 1). The study is based on both tolerance and clinical efficacy as proposed by Bryant and Day’s which allows simultaneous evaluation of clinical response and toxicity [13].

**Fig. 1 Fig1:**
[figure not shown]
Methodology design of the STEREO-HBM study

### Study sites

The list of study sites is available on https://clinicaltrials.gov/ct2/show/NCT03696680.

### Study treatment

Each targeted brain metastasis (hemorrhagic or not) will be treated at the dose of 30 Gy in 3 fractions at 10 Gy/fraction every 2 days [19, 20]. All target lesions (maximum 3 brain metastases plus one tumor bed) will be treated as much as possible over 1 week. However, cerebral irradiation of all the lesions may be spread over 7–10 calendar days. The irradiation facility could be LINAC (Truebeam STX®, Versa HD®, Novalis® …) or robotic radiosurgery system (Cyberknife®).

A minimum of 95% of the target volume (PTV) should receive at least 95% of the total prescribed dose of 30Gy (V95 > 28.5Gy).

The target volumes will be defined as [21, 22]:
GTV (Gross tumor volume): Gadolinium enhanced volume or surgical tumor bedCTV (clinical target volume) = [GTV + 1 mm]SM (set-up margins) = 1–2 mm according to the technique or irradiation system usedPTV (planning target volumes) = CTV + SM

Organ at risk will be delineated according to investigator habits (Optic chiasm, Optic nerves, Brainstem, Cochlea, Spinal Cord, Eyes). The prescription isodose percentage should be higher than 70%.

### Study procedures

The trial schema is illustrated in Fig. 2. The overview of study assessments and procedures are detailed in Table 2.

**Fig. 2 Fig2:**
[figure not shown]
Schematic representation of the STEREO-HBM study. *Each targeted brain metastasis (hemorrhagic or not) will be treated at the dose of 30 Gy in 3 fractions at 10 Gy per fraction every 2 days. All target lesions (maximum 3 brain metastases plus one tumor bed) will be treated as much as possible over 1 week. However, cerebral irradiation of all the lesions may be spread over 7–10 calendar days. **Standard MRI imaging protocol plus optional multivoxel spectroscopy imaging (MSI) only for voluntary patients with specific signed informed consent. Abbreviation: FSRT hypofractionated stereotactic radiotherapy; MRI Magnetic Resonance Imaging. *Each targeted brain metastasis (hemorrhagic or not) will be treated at the dose of 30 Gy in 3 fractions at 10 Gy per fraction every 2 days. All target lesions (maximum 3 brain metastases plus one tumor bed) will be treated as much as possible over 1 week. However, cerebral irradiation of all the lesions may be spread over 7–10 calendar days. **Standard MRI imaging protocol plus optional multivoxel spectroscopy imaging (MSI) only for voluntary patients with specific signed informed consent. Abbreviation: FSRT hypofractionated stereotactic radiotherapy; MRI Magnetic Resonance Imaging

**Table 2 Tab2:** Table caption

	Before initiation of treatment D-15 to D0	Stereotactic irradiation week FSRT Treatment of all lesions in 7-10 days maximum	End of irradiation W1 (1 week after the end of irradiation)	Follow-up visits after treatment				Follow-up after progression^f^
				Each week up to 2 months after end of treatment W2 to W9	4 months after end of treatment W16	6 months after end of treatment W24	Every 3 months up to disease progression^c^	
Stereotactic irradiation		Each brain metastasis (hemorraghic or not) will be treated at 30 Gy in 3 fractions of 10 Gy / fraction every 2 days on maximum 7 days						
Signature of informed consent	✓							
Clinical exam including:								
- Disease medical history, weight, height, SC, PS) Patient pronostic (DS-GPA)	✓							
- Complete clinical evaluation and neurological examination		✓	✓	✓	✓	✓	✓	
- Evaluation of toxicities		✓(once a week)	✓	✓	✓	✓	✓	✓
Biological assessment^a^								
- Complete Blood Count	✓		✓	✓	✓	✓	✓	
- Creatinin-^**a**^	✓		✓	✓^b^	✓	✓	✓	
Imagery including:	✓							
- Cerebral scan	✓		✓	✓^b^	✓	✓		
- Cerebral MRI with T1 sequency Followed by Spectro-MRIe (ancillary study)	✓	✓ (in case of neurological degradation due to treated lesions)	✓	✓^b^	✓	✓	✓ ✓	
Quality of life questionnaires (EORTC QLQ C30 and BN20)	✓			✓ Only at 1 month	✓	✓	✓^d^	

^a^Creatinin must be performed before MRI

^b^4 weeks and 8 weeks after the end of irradiation (W4 and W8)

^c^Every 3 months up to at least one target irradiated lesion in disease progression

^d^only every 6 months

^e^Spectro-MRI is performed at the same time of standard cerebral MRI and only applies to patients who have given their signed consent

^f^After progression, a survival status will be collected every 3 months with persistent toxicities due to radiotherapy

#### Brain tumor evaluation

Brain tumoral evaluation will be in line with international guidelines [23]. It will be based on a brain MRI performed at baseline (before FSRT), at 1 week, 4 weeks, 8 weeks after the end of FSRT and thereafter at 4 months, 6 months and every 3 months post-FSRT in the absence of tumoral progression.

Each brain MRI will include the following sequences [19, 24, 25]: T1, T2, T2*, T1 with gadolinium and T2 FLAIR, and, if possible, MRI SWI (susceptibility-weighted imaging).

Disease assessment evaluation will be determined locally according to RECIST version 1.1 criteria.

#### Multi-modality MRI ancillary study

In addition to the standard MRI imaging protocol, each MRI imaging evaluation will include an optional multivoxel spectroscopy imaging (MSI) that will be performed only for voluntary patients with specific signed informed consent.

Perfusion and diffusion sequences will be added [26–28]. Evaluations may be helpful to explore the biochemistry of the tumor. Indeed, it appears important to be able to differentiate a tumor relapse from a therapeutic effect (radionecrosis) in the setting of this FSRT.

#### Quality of life assessment

Each patient will be asked to fil in standardized and validated self-administered questionnaires (EORTC QLQ-C30 and its specific brain cancer module BN-20) to assess health-related quality of life (QoL). QoL will be assessed at baseline, 4 weeks after the end of FSRT, thereafter 4 months, 6 months and every 3 months if no disease progression has occurred.

### Concomitant treatments

Authorized concomitant treatments include bisphosphonates and corticotherapy, prescribed at the discretion of the investigator, according to local practices.

The following treatments are prohibited:
Systemic anticancer drugs (including chemotherapy, hormonotherapy, anti-angiogenics) have to be suspended at least 7 days prior to FSRT initiation and may be reintroduced 7 days after the last fraction.Anticoagulant drugs taken in a curative intent and platelet anti-aggregants have to be suspended at least 5 days prior to FSRT initiation and may be reintroduced 2 months after the end of FSRT

### Statistical design overview

The study will be conducted in 2 steps (a ‘proof of concept’ step followed by a ‘validation’ step) with a two-stage phase 2 design proposed by Bryant and Day [13], combining both safety and efficacy as primary endpoint (Fig. 1).

We posited the following assumptions:
π_T0_ **≥** 0.15 and π_T1_ **≤** 0.05, the unacceptable and expected rate of hemorrhagic complications occurring within 4 months after the end of FSRT, respectivelyπ_R0_ **≤** 60% and π_R1_ **≥** 80%, the unacceptable and expected local control rate of irradiated target lesions at 6 months, respectively.

With an alpha risk of 10% for both the efficacy and the toxicity, and a power of 90%, a total of 41 assessable patients are required.

The continuation of the study will depend on the results of the interim analysis.

Interim analysis will be performed after the first step: 6 assessable patients will be analyzed. Inclusions will not be suspended during the interim analysis. If less than 3 patients are locally controlled at 6 months or if 2 or more patients have presented an intracerebral hemorrhagic toxicity within 4 months, then the study will be discontinued for futility. If 2 or more patients reported intracerebral hemorrhagic toxicity before the end of the first step, the study would be terminated early for excess of toxicity. Otherwise, the study could continue into the second step: 35 additional assessable patients will be needed.

Final analysis will be performed after the second step. After a 6-month follow-up of the 41 assessable patients, if less than 29 patients are locally controlled at 6 months, or if 2 or more patients had intracerebral hemorrhagic toxicity within the 4 months following FSRT, then the study will conclude that FSRT (3 x 10Gy over 1 week) is not indicated to treat patients with hemorrhagic brain metastases. Otherwise, that is, if 29 or more patients are locally controlled at 6 months and if 1 patient, at most, reported intracerebral hemorrhage within 4 months post-FSRT, then the study will conclude that FSRT is effective, well tolerated and does not increase intracerebral hemorrhagic toxicity in patients with bleeding brain metastases.

Considering a drop-out rate of 10% (lost to follow-up, protocol deviation, etc.), 7 and 39 patients will be enrolled in the first and second step, respectively, for a total of 46 patients.

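### The final rule of at most 1 haemorrhage in 41 patients gives about 36% power, not the stated 90%, and a toxicity type I error of about 1%, not 10%

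*Protocol article*

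**What the plan says.** All elements stand in one section of the protocol article, Statistical design overview, which describes a Bryant and Day two-stage design.

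- Toxicity hypotheses: "π_T0_ ≥ 0.15 and π_T1_ ≤ 0.05, the unacceptable and expected rate of hemorrhagic complications occurring within 4 months" after the end of FSRT.
- Efficacy hypotheses: 6-month local control of 60% (unacceptable) against 80% (expected).
- Errors and size: "With an alpha risk of 10% for both the efficacy and the toxicity, and a power of 90%, a total of 41 assessable patients".
- First step: "Interim analysis will be performed after the first step: 6 assessable patients will be analyzed". The trial stops on this condition: "If less than 3 patients are locally controlled at 6 months or if 2 or more patients have presented an intracerebral hemorrhagic toxicity".
- Second step: "35 additional assessable patients will be needed", which makes 6 + 35 = 41.
- Final failure: "if less than 29 patients are locally controlled at 6 months, or if 2 or more patients had intracerebral hemorrhagic toxicity within the 4 months".
- Final success: 29 or more controlled and "if 1 patient, at most, reported intracerebral hemorrhage within 4 months post-FSRT".

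The limit of 1 appears in both the failure sentence and the success sentence, and the two agree. It is therefore not an isolated misprint.

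**The concern.** The limit on haemorrhages is the same after 41 patients as after 6. At the rate the plan itself calls expected, 41 × 0.05 = 2.05 haemorrhages are expected, so the average outcome under the design's own favourable hypothesis already fails. An observed 2/41 = 4.9%, just below the expected 5%, would lead to the conclusion that FSRT is not indicated. That cannot fit a power of 90%.

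The trial is meant to resolve a reluctance that the Background describes as resting on unproven bleeding risk. If the rule rejects a treatment that performs as hoped more often than it accepts it, a negative result would say little about that question. The exposure is greater because the safety endpoint, as defined under Primary objective, also counts MRI signal changes that cause no symptoms. Two silent imaging events are enough to fail.

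**Working it through.** **Inputs** (all from Statistical design overview): n1 = 6, n2 = 35, N = 41; control rate p = 0.60 or 0.80; haemorrhage rate q = 0.15 or 0.05; efficacy limits 3 of 6 and 29 of 41; haemorrhage limits 1 of 6 and 1 of 41. Below, b(x; n, p) is the binomial probability of x events in n.

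**1. Efficacy leg**

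P(pass) = Σ over x = 3 to 6 of b(x; 6, p) × P(Bin(35, p) ≥ 29 − x)

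- p = 0.60: 0.1015
- p = 0.80: 0.9355

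This matches the stated 10% error and exceeds the stated 90% power, so the two-stage reading of the design is sound.

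**2. Toxicity leg**

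P(pass) = Σ over y = 0 to 1 of b(y; 6, q) × P(Bin(35, q) ≤ 1 − y)

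Because the final limit equals the interim limit, the interim look adds nothing, and this reduces to P(Bin(41, q) ≤ 1) = (1 − q)^41 + 41q(1 − q)^40.

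- q = 0.05: 0.1221 + 0.2634 = 0.3855
- q = 0.15: 0.0013 + 0.0092 = 0.0105

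**3. Joint figures, endpoints independent**

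- Power at 80% / 5%: 0.9355 × 0.3855 = 0.361
- Toxicity error at 80% / 15%: 0.9355 × 0.0105 = 0.0098
- Efficacy error at 60% / 5%: 0.1015 × 0.3855 = 0.039

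**4. Dependence between endpoints**

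Joint success cannot be likelier than passing toxicity alone, so power is at most 0.3855. It is at least 0.9355 + 0.3855 − 1 = 0.321. Power therefore lies between 32.1% and 38.6%, whatever the correlation.

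**5. Another reading of the limit**

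If at most 1 haemorrhage were allowed in each step separately, the toxicity pass probability at 5% would be P(Bin(6, 0.05) ≤ 1) × P(Bin(35, 0.05) ≤ 1) = 0.9672 × 0.4720 = 0.457. This is still far from 90%.

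**6. How the figures move with the final limit** (6 + 35 patients, all else as stated)

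| Final limit | Toxicity error, toxicity leg alone | Toxicity error, joint | Joint power |
|---|---|---|---|
| ≤1 of 41 (as written) | 1.05% | 0.98% | 36.1% |
| ≤2 | 4.3% | 4.0% | 61.5% |
| ≤3 | 11.4% | 10.6% | 78.4% |
| ≤4 | 22.7% | 21.2% | 86.4% |
| ≤5 | 36.7% | 34.3% | 89.4% |
| ≤6 | 50.4% | 47.2% | 90.2% |

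Joint power reaches 90% only where the toxicity error is about one half.

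**7. Can any design with 41 patients meet the claim?**

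Over every first-step size and every pair of haemorrhage limits at N = 41, the highest toxicity pass probability at 5% with toxicity error no more than 10% is 80.6%. Since joint power cannot exceed this, 90% is out of reach.

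**8. What would meet it?**

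- A single-stage toxicity test at 10% / 90% first becomes possible at 60 patients (≤5 of 60: error 9.7%, power 92.1%).
- A search over two-stage joint designs under independence, with joint error definitions, gives 59 as the smallest total (errors 7.9% and 9.98%, power 90.1%).
- With the rule as written, joint power reaches 90% only if the true haemorrhage rate is about 0.75%.

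**The case against.** The strongest reply is that an alpha of 10% is a ceiling. An attained 1% respects it, and a strict safety limit for intracerebral bleeding may be deliberate. This stands as far as it goes: patients are not under-protected, and the low toxicity error is a symptom of the strict limit. It does not rescue the power statement, which is wrong under the printed rule whatever the motive.

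It can also be said that the cause is unknown. The document shows only that the interim and final limits are the same count. The slip could lie in the limit, the rates, the error levels or the sample size. That is fair, and no particular cause is asserted here.

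The choice of haemorrhage limit is, moreover, a safety judgement and not purely arithmetic. That stands too. The table in the working shows what each limit implies and does not recommend one.

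Finally, a failed trial leads to the statement that FSRT is not indicated, which is not literally a finding of harm. But the matching success statement speaks of good tolerance and no increase in bleeding, so a failure on the haemorrhage limit will be read as a safety result.

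**Conclusion.** The point holds. The stated 90% power is wrong for the stated rule: joint power is 36.1% under independence, with a range of 32.1% to 38.6% over all possible dependence. The toxicity type I error is 1.05% for the toxicity leg alone (0.98% jointly), against a stated 10%. A treatment with exactly 80% control and 5% haemorrhage fails in about 64% of trials (1 − 0.361), almost entirely because of the haemorrhage limit.

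The result rests on exact binomial probabilities, 41 assessable patients and the rule as printed. It does not depend on any outside figure. An analysis plan could not fill the gap, because the rates, errors, size and rule are all fixed here and are mutually incompatible. It must be fixed before the result is interpreted.

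**What to change.** Amend the Statistical design overview so that rates, error levels, sample size and final haemorrhage limit agree, and print the exact operating characteristics beside the rule, stating whether they are joint or per endpoint.

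- **Keep 41 patients and the present limit.** Replace the 10% / 90% statement with the true figures: joint power 36.1%; toxicity error 1.05% for that leg alone (0.98% jointly); efficacy error 10.2% for that leg alone (3.9% jointly).
- **Keep 41 patients and re-derive the limit from 15% / 5%.** State the resulting figures from the table. The limit of 3 comes closest to the stated 10% toxicity error but slightly exceeds it, with power of 78.4%. Which limit is acceptable is for the sponsor and the IDMC to decide.
- **Keep 10% / 10% / 90%.** The sample size must then rise to about 59 assessable patients with new limits at both steps, or the rates must be revised.

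Under either of the first two options the 90% claim is removed. The cost is one amended paragraph and no added patients, but the stated power becomes less favourable. Changing the limit would alter the success criterion and so needs IDMC review.

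### No haemorrhage bound acts during the second step, although the final rule is already failed beyond recovery at the second event

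*Protocol article*

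**What the plan says.** All the rules stand in the Statistical design overview of the protocol article.

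- First step: "6 assessable patients will be analyzed". The trial stops on efficacy "If less than 3 patients are locally controlled at 6 months", or on bleeding "if 2 or more patients have presented an intracerebral hemorrhagic toxicity within 4 months, then the study will be discontinued for futility".
- A separate sentence allows a stop before that look, for the first step only: "If 2 or more patients reported intracerebral hemorrhagic toxicity before the end of the first step, the study would be terminated early".
- Accrual goes on meanwhile: "Inclusions will not be suspended during the interim analysis".
- The second step adds 35 assessable patients. At the final analysis of 41 the treatment is rejected if fewer than 29 are locally controlled, "or if 2 or more patients had intracerebral hemorrhagic toxicity within the 4 months following FSRT".
- Planned enrolment is 7 patients in the first step and 39 in the second.

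The Data monitoring committee section sets up an independent committee to protect patients and weigh benefit against risk. Its role is advisory, the sponsor decides, and no haemorrhage count is attached to it.

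**The concern.** The first-step bound and the final bound are the same cumulative count. A trial that enters the second step with no event or one event has failed for good when its second event occurs, whether that is patient 10 or patient 40. From then on, further patients cannot change the conclusion on safety.

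The plan accepts for the first step that reaching the bound should end the study without waiting for the look. It says nothing equivalent for the second step, which holds most of the exposure. The Background gives bleeding as the reason clinicians hesitate to use this treatment here, so patients would be exposed to the risk of main concern after the trial had answered its safety question.

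**Working it through.** **Inputs (Statistical design overview).** Haemorrhage rate 15% unacceptable, 5% expected; local control 60% and 80%; 6 + 35 = 41 assessable patients; continue with at least 3 of 6 controlled and at most 1 of 6 with haemorrhage; succeed with at least 29 of 41 and at most 1 of 41. The 10% rate below is an intermediate value added here. Accrual of 1, 2 or 4 patients a month is assumed, because the article gives no rate.

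**1. The plan's own figures.** The dropout allowance reproduces: 6/0.9 = 6.7, so 7; 35/0.9 = 38.9, so 39; 41/0.9 = 45.6, so 46. The efficacy bounds give alpha 10.15% and power 93.6%. The stated 90% power does not reproduce. Because at most 1 of 41 implies at most 1 of 6, the chance of accepting on haemorrhage is P(Bin(41, p) ≤ 1):

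- p = 0.05: 0.95^41 + 41 × 0.05 × 0.95^40 = 0.122 + 0.263 = 38.6%
- p = 0.15: 0.85^41 + 41 × 0.15 × 0.85^40 = 0.0013 + 0.0092 = 1.05%

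With the two endpoints taken as independent, joint power is 0.936 × 0.386 = 36.1%. Whatever their association, it cannot exceed 38.6%.

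**2. How often the gap is entered.** The six-patient look stops with probability 1 − (1−p)^6 − 6p(1−p)^5. The chance of passing it and later failing on haemorrhage is 1 − stop − accept.

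**3. Where the second event falls.** It falls at patient k with probability (k−1)p²(1−p)^(k−2). The mean is taken over k = 7 to 41.

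| True rate | Stopped at 6 | Accepted | Pass, then fail | Mean position of second event | Still to come of 41 |
|---|---|---|---|---|---|
| 5% | 3.3% | 38.6% | 58.2% | 23.9 | 17.1 |
| 10% | 11.4% | 7.4% | 81.2% | 19.2 | 21.8 |
| 15% | 22.4% | 1.05% | 76.6% | 15.5 | 25.5 |

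**4. Expected number treated at 15%, haemorrhage rule only.** As printed, with no lag and no overrun: 6 × 0.2235 + 41 × 0.7765 = 33.2. Stopping at the second event with instant detection: E[min(T, 41)] = 13.3, where T is the position of that event. If every event is seen a full 4 months late, E[min(T + 4a, 41)] applies at accrual a per month. The like-for-like printed plan then carries 6 months of accrual beyond the six patients: (6 + 6a) × 0.2235 + 41 × 0.7765.

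| Accrual per month (assumed) | Printed plan with overrun | Stop at second event, 4-month lag |
|---|---|---|
| 1 | 34.5 | 17.2 |
| 2 | 35.9 | 21.1 |
| 4 | 38.5 | 28.6 |

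**5. Efficacy counterpart.** 41 − 29 + 1 = 13: once 13 assessable patients are not controlled, 29 of 41 is out of reach.

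**6. Which patients to count.** If all 46 enrolled were counted, P(at most 1 event) would be 32.3% instead of 38.6% at 5%, and 0.52% instead of 1.05% at 15%. Only a count in assessable patients reproduces the final rule.

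**The case against.** Looks only at the end of each stage are the normal form of a Bryant-Day design, and stopping early once the result is settled is an optional refinement. The committee can advise a stop at any time, and the full protocol or committee charter, not shown, may contain more. This stands as far as it goes: the article contains no contradiction here, and it would be too much to infer that accrual must run to 41 whatever happens. But this article already departs from stage-end looks in the first step, and the committee's advisory role does not supply a bound for the second.

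A reader might also infer that the first-step early stop has no denominator, so that two events among, say, 30 patients treated by the time of the look would end the trial. The document does not support that. It fixes the first step at 6 assessable patients, 7 enrolled; patients entered while those outcomes mature belong to the second step. At a 5% rate, two or more events have probability 3.3% in 6 patients and 4.4% in 7. What remains is a wording point.

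It is tempting, too, to quote the fall from 33 to 13 patients as the saving. That needs instant detection. Outcomes can take up to 4 months to appear while accrual continues, although the MRIs at 1, 4 and 8 weeks would shorten the lag.

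Finally, the second event is decisive only because the printed final bound is so tight: at 5%, 41 × 0.05 = 2.05 events are expected. This stands, and limits the size of the point. With a final bound of at most 3, the fourth event (capped at 41, that bound alone) would come on average at patient 25.5 at 15%, and accrual would end at 29 to 37 with the lag.

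**Conclusion.** The gap is real under the rules as printed. At 15%, 77% of trials would pass the first look and then fail on haemorrhage, with about 25 of 41 assessable patients still to come at the deciding event; at the expected 5%, 58% and about 17. Those counts are upper limits on the patients who could be spared. At 15% the expected number treated falls from 33 to 13 with instant detection, or to about 17, 21 or 29 with the full lag at the assumed accrual rates.

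The figures rest on independent patients with a constant event rate and on the printed bound of two. The mismatch of that bound with the 5% and 15% rates and 90% power is a larger and separate fault: adding this stop to the bound unchanged would end 61.4% of trials (1 − 0.386) for haemorrhage at the expected rate. This point is therefore an inexpensive improvement in patient protection, secondary to repairing the bound.

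**What to change.** First reconcile the final haemorrhage bound with the 5% and 15% rates, the 90% power and the 41 patients. Then add to the Statistical design overview:

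1. Accrual stops, in either step, once the running count of primary-endpoint haemorrhages among assessable patients exceeds the final bound, whatever that bound becomes.
2. Accrual also stops once the 13th assessable patient is not locally controlled, while the final bound is 29 of 41.
3. The first-step early-termination sentence refers to the first-step patients (6 assessable).

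The count must use the same definition of assessable as the final rule, including for a patient who bleeds and is later lost. On that condition the final decision, alpha and power do not change.

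The cost is a few sentences and a running count reported to the data monitoring committee. The downside is fewer patients for the secondary endpoints in a trial that has already failed.

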Although radiosurgery (SRS) or fractionated stereotactic radiotherapy (FSRT) is now the mainstay of treatment for brain oligo-metastases (3–5 metastases), allowing a 12-month local control greater than 75% [8], whole brain radiotherapy (WBRT) still remains the usual treatment of haemorrhagic brain metastases, despite its poor efficacy, namely a 6-month and 12-month local control rate of 37 and 15%, respectively [9]. This attitude is consistent with the report of the French High Authority of Health (HAS) which does not support radiosurgery for the treatment of haemorrhagic brain metastases (HAS report 2001). It is based on the results from a retrospective study (131 metastases on 54 patients) [10]: haemorrhage was identified in 7.4% of the metastases before radiosurgery and in 18.5% of the metastases after radiosurgery. Since this publication, although it did not clearly demonstrate a relationship between radiosurgery and the risk of haemorrhage, FSRT/SRS is suspected to increase the risk of brain haemorrhage. Furthermore, in spite of several reports of intra-tumor haemorrhage after radiosurgery of brain metastases, radiosurgery was not shown to increase the incidence of haemorrhage. Thus, among melanoma patients carrying brain metastases [11], the rate of intra-tumor haemorrhage was shown to be similar before and after treatment by stereotactic Gammaknife (23.7% vs. 15.2%, *p* = 0.89); the presence of intra-tumoral bleeding before treatment was not found to major the risk of bleeding after treatment (*p* = 0.9). According to some authors, the occurrence of post-treatment bleeding would not be related to the achievement of radiosurgery, but rather to the intrinsic sensitivity of the tumor to bleed [12].

Besides these conflicting findings, it has to be highlighted that most of these studies were conducted exclusively with SRS (a single fraction issued) and from either a Gammaknife® or a linear adapted accelerator. To date, there are no specific available data for FSRT (several fractions) with Cyberknife®, a newer technology.

Overall, radiation oncologists generally remain reluctant to deliver FSRT on hemorrhagic brain metastases. Therefore, the standard treatment remains panencephalic irradiation, even if it is clearly not optimal.

In this context, there is a real need to establish a standard management of hemorrhagic brain metastases, notably using more innovative radiotherapy techniques like FSRT.

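### The prespecified positive conclusion claims that FSRT does not raise bleeding, but a single-arm test against a fixed 15% rate can only show that the rate is below 15%

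*Protocol article*

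**What the plan says.** Under Trial design, the protocol article describes a trial without a comparator: "The STEREO-HBM study is a multicenter 2-step non-randomised phase II trial where 46 patients are planned to be enrolled". Under Primary objective, the safety endpoint is the proportion of patients in whom at least one target metastasis has a bleeding complication in the 4 months after FSRT. It is an absolute proportion, not a contrast.

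The Statistical design overview sets two fixed values for it, 15% and 5%, labelled "the unacceptable and expected rate of hemorrhagic complications occurring within 4 months after the end of FSRT". The efficacy values are 60% and 80%, labelled "the unacceptable and expected local control rate of irradiated target lesions at 6 months". Neither safety value is described as a rate under WBRT or without irradiation.

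The same section ties the final result to a fixed verdict. With 29 or more of 41 patients controlled and no more than one haemorrhage, the study is to conclude that "FSRT is effective, well tolerated and does not increase intracerebral hemorrhagic toxicity in patients with bleeding brain metastases".

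**The concern.** The words effective and well tolerated can be read against the fixed thresholds. The claim of no increase cannot, because it needs the rate that the same patients would have had without FSRT. The design neither measures that rate nor borrows it from a stated source.

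This matters because the Background presents exactly this question as the reason for the trial. Suspicion that stereotactic irradiation raises bleeding risk is what keeps clinicians from using it, and the retrospective series behind that suspicion is itself said not to have demonstrated a relationship clearly. The decision rule would let an uncontrolled trial declare the opposite causal claim as its formal primary conclusion. It is a prespecified verdict of the primary analysis, not a remark in the Discussion, so it would be expected to carry into the trial report.

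**Working it through.** **1. Is there a comparator anywhere in the article?**
- Concurrent arm: none (Trial design).
- Fixed reference: 15% is the unacceptable rate and 5% the expected rate. Both refer to patients after FSRT (Statistical design overview).
- Patients' own baseline: Table 1 requires signs of intra-tumour bleeding in at least one metastasis before irradiation. Baseline bleeding is therefore 100% by selection, and a before/after comparison cannot show whether FSRT adds bleeding.
- Literature (Background): one series reports 7.4% of metastases before and 18.5% after radiosurgery. It counts metastases, while the endpoint counts patients. In the other series "the rate of intra-tumor haemorrhage was shown to be similar before and after treatment by stereotactic Gammaknife" (23.7% against 15.2%, p = 0.89), but it is in melanoma, which Table 1 excludes. Neither gives a 4-month rate per patient without FSRT in this population.

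**2. The plan's own figures.** The sentence on sample size reads, up to its last word: "With an alpha risk of 10% for both the efficacy and the toxicity, and a power of 90%, a total of 41 assessable patients are". I computed exact two-stage binomial probabilities with 6 + 35 patients.
- Efficacy (at least 3 of 6, then at least 29 of 41): probability of passing 0.1015 at 60% and 0.936 at 80%. This is close to the stated 10% and 90%.
- Safety (at most 1 of 6, then at most 1 of 41): 0.0105 at 15% and 0.386 at 5%. This does not match the stated 10% and 90%. It is a separate matter that needs its own reconciliation, and the present point does not depend on it.

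**3. What the best evidence from a pass supports.** Exact (Clopper-Pearson) upper limit for x events in n at one-sided level 1 − a: the (1 − a) quantile of Beta(x + 1, n − x).

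| Events | 90% one-sided | 95% one-sided |
|---|---|---|
| 0/41 | 5.5% | 7.0% |
| 1/41 | 9.2% | 11.1% |

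For 1/41 (2.4%) the two-sided 95% interval is 0.06% to 12.9%. All these upper limits lie below 15%, so a statement against 15% is supported. None of them refers to a rate without FSRT.

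**4. How often the safety rule passes.** The interim safety stop (2 or more of 6) is already implied by the final limit of 1 of 41. Hence P(pass) = (1 − p)^41 + 41 · p · (1 − p)^40.

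| True rate after FSRT, p | First term | Second term | P(pass) |
|---|---|---|---|
| 1% | 0.662 | 0.274 | 0.94 |
| 2% | 0.437 | 0.365 | 0.80 |
| 3% | 0.287 | 0.364 | 0.65 |
| 5% | 0.122 | 0.263 | 0.39 |
| 10% | 0.013 | 0.061 | 0.07 |

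The rate without FSRT does not appear in this formula. Whatever it is, the rule gives the same answer. As an illustration only, if that rate were 1% (an assumption), a rise to 3% would pass safety with probability 0.65 and a rise to 5% with probability 0.39. Where the efficacy criterion is also met, no increase would then be declared.

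**5. Local control at the boundary.** For 29/41 (70.7%), the exact one-sided lower limit, the a quantile of Beta(29, 13), is 59.8% at 90% and 56.9% at 95%. A pass at the boundary therefore does not quite establish that control exceeds 60%, and the replacement wording has to respect this.

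**The case against.** **The fault is only in the wording.** The stated objective is an absolute proportion. Endpoint, thresholds, sample size and stopping rules would not change, and the sentence could be corrected at reporting. That is true of the cost. But the sentence is the plan's formal conclusion, and it is stated rather than left to an analysis plan.

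**A within-patient baseline exists.** MRI is done before FSRT and serially afterwards, and the safety endpoint rests on changes in MRI signal, so the clause may loosely mean no worsening from baseline. The baseline is real, but because bleeding is an entry criterion it cannot show what would have happened without FSRT.

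**The rule is strict.** At true rates of 9% and 11% it passes with probability only 0.106 and 0.051, and at 18.5% with 0.002. This stands. A clearly high rate is unlikely to pass, and the weakness lies at low rates.

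**Stronger readings that the article does not support:**
- A reader might infer that a pass would conceal a large increase over a specific low background. No background rate is given, so the size of any hidden increase is unknown. Against 7.4% (per metastasis, illustrative only), 9% to 11% would be a modest difference.
- A reader might infer that FSRT does raise bleeding. The cited series do not settle this, and the melanoma figures do not apply to the population here.
- A reader might infer that a single-arm phase II trial is unsuitable, or that the negative conclusion has the same fault. The design is legitimate for testing fixed rates, and the negative conclusion makes no comparative claim.

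**Conclusion.** The positive conclusion is wrong as written. The trial can show that the 4-month haemorrhage rate is below the prespecified 15%. It cannot show that FSRT leaves the rate unchanged, because no reference rate exists in the design or in the article.

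With the largest number of events that still passes, 1/41, the data exclude rates above 9.2% (90%) or 11.1% (95%). The pass probabilities of 0.94 at a true 1%, falling to 0.39 at 5% and 0.07 at 10%, show that an increase over a low background could be reported as none. Whether that would happen depends on a rate the article does not give, so no size can be put on the error. The finding itself rests on no assumed rate. The calculations assume independent patients with a common probability of bleeding and all 41 assessable.

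**What to change.** In the Statistical design overview, delete the clause claiming no increase in haemorrhagic toxicity. In its place:
- Conclude that the prespecified safety and efficacy criteria were met: the 4-month haemorrhage rate is below the unacceptable 15%, and the local control criterion set against 60% was met. Do not write that control exceeds 60%, since the 90% lower limit at 29/41 is 59.8%.
- Report both rates with exact confidence limits.
- State that bleeding was not compared with WBRT or with no irradiation.

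The change is confined to one decision paragraph. Sample size, endpoints, conduct and treatment stay the same. The cost is a more modest claim, which leaves open whether FSRT changes bleeding risk.
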